## Study Plan

---

### Background

Stroke is a common disorder worldwide and hemiparesis is the most common acute impairment and often impacts on gait function (Duncan 2005, Jorgensen 1995). While motor control is improved in most patients during the months following the ictus, a substantial proportion are left with impaired mobility. Even though several studies indicate that early, intensive training of motor functions may accelerate postacute recovery and improve the final outcome there is a recognised need for more effective treatment in this respect (Langhorne 2009).

Several studies have explored the value of various technologies that are designed to enable more intensive gait training programs (Mehrholtz 2012). While there is evidence that body weight supported gait training on a treadmill may be beneficial early after stroke (Moseley 2005), there is a need for more studies to demonstrate the additional value of training supported by electromechanical devices, which may not only enable more intensive training but also more efficient utilisation of therapist time.

Devices used to support gait training after stroke include treadmill training with or without body weight support (BWS). These devices may be combined with electromechanical “gait machines”, which can allow more reproducible gait movements when compared to when a therapist move the patients legs. Gait machines are often categorized as machines using an end-effector principle and machines that function as exoskeletons (Hesse 2010). Machines based on the end-effector principle use foot plates that move the feet in a controlled gait pattern and allow the operator to adjust many aspects of locomotion, such as speed, stride length and step height. In contrast, exoskeletons are attached to the patient and function as an external skeleton. Exoskeletons for lower extremities have joints matching the patient's lower limb joints and motors that drive movements over these joints to assist leg movements. Recent reviews conclude that more data is needed with regard to the optimal type of electromechanical device for stroke patients (Merholtz 2012) and that there is a need for further development of concepts and devices as well as their evaluation in clinical trials (Dobkin 2009, Pennycott 2012).

The Hybrid Assistive Limb has been developed at the University of Tsukuba and Cyberdyne Inc in Tsukuba, Japan, in a group headed by professor [name] (Kawamoto 2009, Kawamoto 2010). The exoskeleton provides support according to the patient's condition by a control algorithm and supporting devices, where each joint (left and right hip and left and right knee) can be controlled separately. HAL offers a hybrid control algorithm consisting of “Cybernic Voluntary Control”, based on the users voluntary muscle activation and bioelectrical signals, such as by electromyographical input, and a “Cybernic Autonomous Control”, based on the users constitution, condition and intensions and using a variety of other signals such as mechanical input. HAL offers a new principle

## Study Plan

---

and allows training early after stroke as soon as postural control is sufficient to allow an upright position. Training by use of HAL may be performed with or without BWS. Our group has recently finalised a study that demonstrates the feasibility and safety of HAL for gait training in patients with impairment early after stroke (Nilsson 2013). This has also been demonstrated after other chronic conditions (Kubota 2013).

### Aim and hypotheses of the study

To compare gait function after training with HAL with gait function after conventional gait training as part of an in patient rehabilitation program early after stroke. The primary outcome will be gait performance after the training period and the secondary outcome will be gait performance 6 months after stroke according to the Functional Ambulation Categories. Another outcome will be length of stay in hospital. We hypothesize that training with HAL will improve their gait function significantly more when compared with conventional gait training.

### Study design

A randomized controlled study.

### Patients

Eligible will be patients living in the Stockholm region and who are admitted to the University Department of Rehabilitation Medicine for inpatient rehabilitation early after stroke from January 2014 until December 2014.

Inclusion criteria: less than eight weeks since stroke; unable to walk independently due to lower extremity paresis (i.e. Functional Ambulation Categories (FAC score 0-1) with or without somato-sensory impairment and with or without spasticity; able to sit on a bench with/without supervision at least five minutes; sufficient postural control to allow upright position in standing with aids and/or manual support; ability to understand training instructions as well as written and oral study information and to express informed consent; body size compatible with the HAL suit.

Exclusion criteria: contracture restricting gait movements at any lower limb joint (hip, knee, ankle); cardiovascular or other somatic condition incompatible with intensive gait training; severe, contagious infections (e. g. with Methicillin Resistant Staphylococcus Aureus (MRSA) or Extended Spectrum Beta-Lactamase (ESBL) bacteria).

### Training program and randomisation

Training with HAL will be performed in one session per day, four days per week during four weeks. HAL will be used according to the manufacturer's manual. Time for each session will be individualised but not exceed 60 minutes/session (effective time). Training with HAL will be performed in combination with body-weight support and treadmill. The training program will be performed by two physiotherapists, who have been trained in the HAL method in Tokyo.

Conventional gait training will be according to current practice, may include use of treadmill and body weight support, and will be documented in the clinical research file (CRF).

Randomisation will be performed by a nurse, who is not otherwise involved in the study according to a block design.

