### Power calculation and statistics

The primary outcome will be the FAC immediately after the training period and at six months after stroke. Based on previous studies of gait recovery early after stroke and of our recent application of HAL early after stroke (Nilsson et al 2013), we estimate that 16 patients per group are needed to demonstrate a clinically meaningful (i.e. one category on the FAC scale) and statistically significant difference between the treatment groups (alpha set at 0.05, power of 80%). Based on our recent experiences, the expected drop out rate is low and we plan to include 36 patients (18/group). The estimated time period for inclusion of all 36 patients is 12 months. Descriptive statistics will be used to describe the two groups at baseline, the Mann Whitney U-test will be used to compare outcomes between treatment groups.

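### The plain Mann-Whitney test for FAC ignores entry FAC (0 or 1), which costs power and leaves the result open to chance imbalance, though it does not bias it

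*Protocol*

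**What the plan says.** The protocol's section Patients restricts entry to "Functional Ambulation Categories (FAC score 0-1", so there are two starting levels. Assessments and blinding lists FAC among the measures and schedules assessments at baseline, after training and at six months, so entry FAC will be on record for every patient.

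Power calculation and statistics makes FAC the primary outcome and sets the target at "one category on the FAC scale", with "alpha set at 0.05, power of 80"%. It states "we estimate that 16 patients per group are needed to demonstrate a clinically meaningful" difference, and then "we plan to include 36 patients (18/group"). For the analysis it says that "the Mann Whitney U-test will be used to compare outcomes between treatment groups". No baseline variable is attached to that test.

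Training program and randomisation gives one sentence on allocation: "Randomisation will be performed by a nurse, who is not otherwise involved in the study according to a block design". It does not mention strata, block size, whether block size varies, or when an allocation is released.

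**The concern.** Entry FAC is measured on the same scale as the outcome, and its two levels lie one category apart, which is also the effect the trial is sized to detect. A patient who starts at FAC 1 can be expected to finish higher than one who starts at FAC 0, although the protocol does not say by how much. As far as the document states, this variable is neither balanced at allocation nor used in the analysis.

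Two things are at stake. First, between-patient variation that the baseline could explain stays in the comparison and lowers power in a trial of 36. Second, the arms may differ by chance in their share of FAC 1 starters, and the named test has no means of allowing for that.

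**Working it through.** **Inputs from the protocol.** 36 patients, 18 per group; 16 per group needed; difference of 1 category; alpha 0.05; power 80%; entry FAC 0 or 1.

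**Assumptions (not in the protocol).** Split of entry FAC: 18, 12 or 9 of 36 at one level. Effect of entry FAC on final FAC: 0.5, 1 or 1.5 categories. SD: see step 1. Two-sided test.

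**1. The plan's own figure.** No SD is given. Solving n = 2(SD × (1.960 + 0.842)/1)² for n = 16 gives SD = √(16/2)/2.802 = 1.01. So 16 per group is consistent with a total SD of about 1.0. The increase from 32 to 36 patients allows for 1 − 32/36 = 11% loss.

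**2. Chance imbalance.** With 18 of 36 at FAC 1 and arms of 18, the number X of FAC 1 starters in one arm is hypergeometric. Its variance is 18 × 0.5 × 0.5 × 18/35 = 2.31, so its SD is 1.52. The arms differ by 2X − 18, with SD 3.04 patients, or 3.04/18 = 0.17 as a proportion.

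| At one level | Differ by 4 or more | Differ by 6 or more |
|---|---|---|
| 18 of 36 | 32% | 9% |
| 12 of 36 | 29% | 7.5% |
| 9 of 36 | 12% | 2% |

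Unstratified blocks do not change this: for an even split, simulated block sizes from 2 to 36 all gave 31–33% for a difference of four or more.

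**3. Effect on the estimate.** Shift = (difference in patients/18) × baseline effect. For four patients this is 4/18 × 1 = 0.22 category if baseline carries over fully, and 0.11 to 0.33 for effects of 0.5 to 1.5. The target is 1.

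**4. Power under the existing, unstratified allocation.** Simulated FAC on integers 0–5, 18 per arm, even split, true difference one category:

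| SD assumption | Baseline effect | Plain Mann-Whitney | Stratified by baseline FAC |
|---|---|---|---|
| Residual SD 1.0 | 0.5 | about 75% | about 77% |
| Residual SD 1.0 | 1 | about 70% | about 77% |
| Residual SD 1.0 | 1.5 | about 60% | about 77% |
| Total SD 1.0 | 1 | about 77% | about 86% |

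The first three rows add the baseline effect to the residual variance. Total SD is then √(1 + effect²/4), which is 1.03, 1.12 and 1.25. The last row keeps the total SD that step 1 implies.

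**5. Type I error.** Over all unstratified allocations, both tests hold about 5%. If the allocation is stratified by entry FAC but the plain test is kept, its error falls to about 2–3% at a one-category baseline effect.

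**6. Stratified allocation on top of the stratified test.** This adds at most about 2 points of power.

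**7. Predictability, if block size is fixed and known and past allocations are tracked.** Blocks of 2, 4 and 6 make 18, 12 and 9 of 36 allocations certain.

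**The case against.** **Chance imbalance is noise that alpha already covers.** This stands. A reader might infer that the plain test is biased or that its error rate is inflated. One can pick out the roughly 16% of allocations with four or more extra FAC 1 starters on HAL and find that, with no true effect, the plain test favours HAL in about 8% of them (one-category baseline effect), against a nominal 2.5%. The tilt is equally likely the other way, and the overall error is about 5%. A four-patient imbalance moves the estimate by about 0.2 category, so it does not by itself create a difference of the target size.

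**The randomisation is the problem.** A reader might infer a single list with one fixed block size, and so many guessable allocations. The protocol says only that a block design is used. Block size is often kept out of a protocol on purpose, and the nurse who randomises has no other role in the study. Past allocations would be visible, since HAL is a worn device in one department, and eligibility involves judgement ("sufficient postural control to allow upright position in standing with aids and/or manual support"). The counts in step 7 still require staff to know the block size. Varying it also changes little for best guesses: about 71% correct with fixed blocks of 4, 69% with mixed blocks of 4 and 6. Only the conditional statement survives.

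**Baseline adjustment belongs in the statistical analysis plan.** That plan may exist and may adjust. The protocol nevertheless names the test, and the test it names is unadjusted, so the sentence should be corrected where it stands.

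**The power loss depends on assumptions.** This stands in part. The fall to 60% goes with a total SD of 1.25, larger than the sample size implies. Holding total SD at 1.0 leaves the plain test at about 77%, but the stratified test then reaches about 86%, so the gain remains.

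**Conclusion.** The point holds as one about efficiency and robustness of the named analysis. The plain Mann-Whitney test discards a baseline value that the trial already collects on the outcome scale. Under the existing allocation, the stratified test gains about 2, 7 and 17 points of power for baseline effects of 0.5, 1 and 1.5 categories at residual SD 1.0, and about 9 points for a one-category effect at total SD 1.0. It also protects the result against an imbalance of four or more FAC 1 starters, which has probability 12% to 32% over the splits examined.

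These sizes rest on the assumed split, baseline effect and SD, none of which the protocol gives. If entry FAC hardly predicts final FAC, the gain is small. That entry FAC is absent from the named test does not depend on these assumptions. The document does not support a claim of systematic bias, of inflated overall type I error, or of allocations that are in fact guessable.

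**What to change.** **Main change.** In Power calculation and statistics, replace the plain test for FAC with wording such as: 'FAC will be compared between groups with the Mann-Whitney test stratified by baseline FAC (0 or 1; van Elteren test).' This needs no extra patients, visits or data. If a separate analysis plan exists, it should name the same test.

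**Optional and secondary.** Stratify the block list by baseline FAC (0 or 1). This makes the balance visible to readers but adds little power. The cost is two short lists instead of one, and arms that may end slightly unequal because of incomplete last blocks. Do it only together with the stratified test, because the plain test would then be conservative.

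**Allocation wording.** In Training program and randomisation, state that block sizes vary and are withheld from recruiting and treating staff, and that each allocation is released only after consent and the baseline assessment are recorded. The sizes themselves need not appear in the protocol. The cost is a sentence or two.

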## Study Plan

---

### Assessments and blinding

Assessments will be performed by a senior consultant physician (specialist in Rehabilitation Medicine), and by a blinded, registered physiotherapist. All data will be documented by use of standardised forms (paper and pencil) for impairments, activity performance/participation, Quality of Life, and by use of a preformed questionnaire on patients' perceptions and a preformed protocol for adverse events and be kept in individual CRFs.

Standard measures will be used for clinical assessments at baseline, immediately after the training period, and six months after the stroke.

*Impairments* will be assessed by use of the NIH Stroke Scale (Lyden 1994) for neurological impairments, Fugl-Meyer Scale (FM-LE) (Fugl-Meyer 1975) and the Modified Ashworth Scale (Bohannon and Smith 1987) for the lower extremities.

*Activity performance, Participation and Quality of Life* will be assessed by use of Functional Ambulation Categories (Holden 1984) (will be performed once a week), 2 minutes walk test in self-preferred speed, Bergs Balance Scale (Berg 1989, 1992), Barthel Index (Mahoney 1965) and EQ5D (Rabin 2001).

*Adverse events* (such as irritated skin, pain, falls) will be documented continuously in the study protocol according to a specific study form.

*Patients' perception* of training will be assessed by a questionnaire.

Study documents will be archived at the study site (University Department of Rehabilitation Medicine) according to current routine during 10 years.

### Power calculation and statistics

The primary outcome will be the FAC immediately after the training period and at six months after stroke. Based on previous studies of gait recovery early after stroke and of our recent application of HAL early after stroke (Nilsson et al 2013), we estimate that 16 patients per group are needed to demonstrate a clinically meaningful (i.e. one category on the FAC scale) and statistically significant difference between the treatment groups (alpha set at 0.05, power of 80%). Based on our recent experiences, the expected drop out rate is low and we plan to include 36 patients (18/group). The estimated time period for inclusion of all 36 patients is 12 months. Descriptive statistics will be used to describe the two groups at baseline, the Mann Whitney U-test will be used to compare outcomes between treatment groups.

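### Six-month FAC is a secondary outcome in the aims but a primary outcome in the statistics section, and the single sample size shows no allowance for a second primary time point

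*Protocol*

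**What the plan says.** The protocol defines its primary outcome in two places.

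- Under Aim and hypotheses of the study: "The primary outcome will be gait performance after the training period and the secondary outcome will be gait performance 6 months after stroke". That sentence goes on to name the Functional Ambulation Categories as the measure.
- Under Power calculation and statistics: "The primary outcome will be the FAC immediately after the training period and at six months after stroke".

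The second section then gives one set of design figures. The target is a difference of one FAC category, with "alpha set at 0.05, power of 80" per cent, and "we estimate that 16 patients per group are needed". Planned enrolment is 36, or 18 per group, to cover a drop-out rate described only as low. The stated basis is earlier work: "Based on previous studies of gait recovery early after stroke and of our recent application of HAL early after stroke". No SD or FAC distribution is given, and alpha is not said to be one- or two-sided. For the analysis, "the Mann Whitney U-test will be used to compare outcomes between treatment groups". The section does not say which time point the power refers to, or whether success requires one time point or both.

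**The concern.** The same measure at the same time point has two different ranks. Both statements are current text, so one does not supersede the other.

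The rank decides what the trial may claim. Suppose FAC does not differ significantly after training but does at six months. Under the aims section the primary outcome has failed. Under the statistics section the same data could be reported as a positive primary result. In the reverse case the aims section gives a positive trial, while the statistics section gives no agreed conclusion. Such a split is plausible, because one assessment follows a four-week programme and the other comes at six months after stroke, when an early difference may have persisted or disappeared.

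The error rate and the power are also at stake. Two primary tests at an undivided 0.05 either inflate the type I error or cost power, depending on a success rule that the text does not give.

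**Working it through.** **Inputs from the protocol (Power calculation and statistics).** Difference 1 FAC category; alpha 0.05; power 80%; 16 per group needed; 18 per group enrolled. **Assumed:** two-sided testing, normal approximation, and a correlation between the two test statistics, for which the protocol gives no value.

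**1. The plan's own figure.** For one test, n per group = 2·SD²·(1.960 + 0.842)² / 1² = 15.70·SD². The SD is missing, so 16 cannot be strictly reproduced. Solved backwards, SD = √(16/2) / 2.802 = 1.01 category. Solved forwards:

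| Assumed SD | n per group, one test at 0.05 | n per group, 0.025 per test |
|---|---|---|
| 0.8 | 11 | 13 |
| 0.9 | 13 | 16 |
| 1.0 | 16 | 20 |
| 1.2 | 23 | 28 |
| 1.5 | 36 | 43 |

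So 16 is the ordinary answer for one two-sided primary test with an SD of about 1. At SD 1.0 a t-test calculation gives 17, and dividing by 0.955 for the Mann-Whitney test also gives 17; both are close to the plan's figure.

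**2. Either time point sufficient, each at 0.05.** Family-wise error = 1 − P(|Z₁| < 1.96 and |Z₂| < 1.96). Under independence this is 1 − 0.95² = 9.75%. From the bivariate normal distribution:

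| Assumed correlation | Family-wise error |
|---|---|
| 0 | 9.75% |
| 0.5 | 9.1% |
| 0.8 | 7.8% |
| 0.9 | 7.0% |

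**3. Power if there are two primary tests.** Take the plan at its word: 16 per group gives exactly 80% for one test, and the effect is equally large at both time points. The expected test statistic is then 1.960 + 0.842 = 2.802 at 16 per group, and 2.802·√(18/16) = 2.972 at 18 per group with no drop-out.

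- One test at 0.05: 80% at 16; Φ(2.972 − 1.960) = 84% at 18.
- Alpha split, 0.025 each: Φ(2.802 − 2.241) = 71% per test at 16; Φ(2.972 − 2.241) = 77% at 18.
- Both required, 0.05 each: joint power is the bivariate normal probability that both statistics exceed 1.960.

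| Assumed correlation | Joint power, 16 per group | Joint power, 18 per group |
|---|---|---|
| 0.5 | 69% | 75% |
| 0.8 | 73% | 78% |

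When both are required, the type I error does not exceed 5%; the whole cost is in power.

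**The case against.** The strongest reply is that the sample size is sound and that the rest depends on choices the protocol has not made. Much of this stands.

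- A reader might infer that the power figure fits neither definition of the primary outcome. The document does not support that. With an SD of about 1 category, 16 per group is the standard result for one primary test, which is what the aims section describes. Since no SD is stated, a misfit to that definition cannot be shown.
- A reader might also infer that the trial runs at a type I error of nearly 10%. That holds only if either time point is enough, and the text does not say so. If both are required, there is no inflation.
- Nor can one say flatly that 16 per group fails to give 80% with two primary outcomes. At SD 0.9, an alpha of 0.025 per test also leads to 16. The losses shown assume that 16 gives exactly 80% for a single test.
- Enrolment is 18 per group, so the figures at 16 apply only once the whole drop-out allowance is used.
- A success rule, an alpha split or a testing order could properly sit in a statistical analysis plan, which is not at hand. Their absence is not the point made here.

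What the reply does not remove is the contradiction. The protocol itself ranks six-month FAC in two incompatible ways, and an analysis plan could follow only one of them.

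**Conclusion.** The point holds as a contradiction about the primary outcome, and it should be settled before any results by group are seen. The design figures are compatible with a single primary test and show no allowance for a second primary time point.

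The statistical consequences are conditional. If either time point suffices, the family-wise error is 7.0% to 9.75% over assumed correlations from 0.9 down to 0. If both are required, joint power is about 69% to 73% at 16 per group and 75% to 78% at 18 without drop-out, for assumed correlations of 0.5 to 0.8. If alpha is split, power per test is about 71% at 16 and 77% at 18. The power figures rest on two-sided testing, on exactly 80% for one test at 16 per group, and on equal effects at both time points. The consequence that needs none of these assumptions is that a split result would be read differently depending on which section is cited.

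**What to change.** Change the first sentence of Power calculation and statistics to match the aims section: the primary outcome is FAC immediately after the training period, tested at two-sided 0.05, and FAC at six months after stroke is a secondary outcome. Add that the 80% power and the 16 per group refer to end-of-training FAC only. Testing six-month FAC only if the primary result is significant is a reasonable option, but it is not needed to remove the conflict.

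This takes a sentence or two in the protocol, with no extra patients or visits and the same sample size. The cost is that the six-month result cannot stand alone as a primary result. If the sponsor prefers to keep both time points as primary, the protocol must state the success rule and justify the sample size again under it, with the assumed SD given.

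### The protocol fixes an unadjusted Mann-Whitney test, leaving prognostic baseline measures unused and giving no estimate on the FAC scale on which the trial is sized

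*Protocol*

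**What the plan says.** The protocol's section on power calculation and statistics names one between-group method: "the Mann Whitney U-test will be used to compare outcomes between treatment groups". Its one stated use of baseline data is that "Descriptive statistics will be used to describe the two groups at baseline". The same section sizes the trial on a difference of "one category on the FAC scale", with 16 patients needed per group and 18 enrolled.

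The section on assessments and blinding provides the baseline information: "Standard measures will be used for clinical assessments at baseline, immediately after the training period, and six months after the stroke". These measures include the NIH Stroke Scale, FM-LE, Modified Ashworth, FAC, a two-minute walk, Berg balance and Barthel.

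Eligibility (Patients section) restricts baseline FAC to 0 or 1 but otherwise allows a broad group: "less than eight weeks since stroke; unable to walk independently due to lower extremity paresis". The section on training and randomisation says only that allocation follows a block design. It mentions no stratification by severity.

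**The concern.** Starting severity and stage of recovery can vary widely among patients enrolled at any time in the first eight weeks after stroke, and both plausibly predict later walking. Neither the allocation nor the analysis uses that information. An unadjusted rank test on 16 to 18 patients per arm leaves all the predictable variation in the error term, and a chance imbalance in severity stays in the observed comparison.

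There is also a mismatch of scale. The trial is designed around one FAC category, but the test as named returns a p-value. A significant result does not show that the difference is near one category, and a non-significant one does not show that a difference of that size is unlikely.

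The matter is worth settling because the design has little slack: the stated sample size gives 80% power only if the SD of FAC is about one category.

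**Working it through.** **Inputs from the protocol.** Target difference 1 FAC category; alpha 0.05; power 80%; 16 per group needed, 18 enrolled. Sidedness is not stated, so two-sided is assumed.

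**Inputs not in the protocol, therefore assumed.** The SD of FAC (0.95 to 1.5 shown) and the correlation r between baseline covariates and later FAC (0.3, 0.5 and 0.6 shown).

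**1. The plan's own figure.** With n = 2(1.96 + 0.84)² × SD² / 1² ≈ 15.7 × SD², SD 1.0 gives 16 per group. Back-solving n = 16 gives SD ≈ 1.01, or 0.99 after allowing for Mann-Whitney efficiency of 0.955. SDs of 1.2, 1.3 and 1.5 would need 23, 27 and 36 per group. So 16 is plausible but cannot be reproduced without an SD.

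**2. Upper guide to the gain.** Adjustment multiplies the error variance by 1 − r²: 0.91, 0.75 and 0.64 at r = 0.3, 0.5 and 0.6. For a normal outcome with exactly 80% unadjusted power (standardised difference 1.024, 16 per arm), dividing 1.024 by the square root of these ratios gives power of 84%, 90% and 94%. This is t-test theory for a continuous outcome. It overstates what a rank method delivers on a six-level scale.

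**3. Simulation on the FAC scale.** A latent normal outcome was cut to 0-5, with a true shift of one category and 16 per arm. The ranges span separate simulations with one or two covariates. With 3,000 runs the Monte Carlo standard error is at most √(0.25/3000) ≈ 0.9 points.

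| Assumed SD | Mann-Whitney | Rank ANCOVA, r = 0.3 | r = 0.5 | r = 0.6 |
|---|---|---|---|---|
| 0.95 | about 77% | 76-79% | 85% | 88% |
| 1.5 | about 41% | 42-45% | 49-51% | 53-55% |

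At SD 0.95 the difference is −1 to +2 points at r = 0.3, then about +8 and +11. At SD 1.5 it is +1 to +4, then +8 to +10 and +12 to +14. Type I error stayed near 5% for both methods. With a single covariate and r = 0, adjusted and unadjusted power were 76.5% against 76.9% (SD 0.95). Two uninformative covariates would cost slightly more.

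**4. Chance imbalance.** Suppose half of all patients have baseline FAC 0. With 18 per arm and two independent Binomial(18, 0.5) counts, the probability that the arms differ by at least 4 patients is 0.243.

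**5. An estimate in FAC categories.** The Mann-Whitney test can be inverted to a Hodges-Lehmann shift and interval, but on six levels the result is coarse. At SD 1.0 with a true shift of 1, the commonest 95% interval was 0 to 2 (about half of runs). With no true effect it was −1 to 1 (about 49%), which does not exclude one category. For a mean difference, the 95% half-width is about t × SD × √(1 − r²) × √(2/16) with t ≈ 2.05:
- SD 1.0: 0.72 unadjusted, 0.63 at r = 0.5.
- SD 1.5: 1.08 unadjusted, 0.94 at r = 0.5.

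At SD 1.0 either interval, if centred on zero, would exclude one category. At SD 1.5 only the adjusted one would, and only just.

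**The case against.** The strongest reply is that a rank test suits an ordinal outcome, is standard, and holds its type I error under randomisation (4-5% in simulation). Alpha already allows for chance imbalance. All of that stands. A reader might infer that the planned test is invalid or that imbalance would bias it; the documents do not support that. Only efficiency and interpretation are at issue.

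Second, covariates, estimates and intervals are commonly left to a statistical analysis plan, which may exist. The protocol does not say that no estimate will be reported. This is fair for the missing interval taken alone. It does not dispose of the point, because the protocol itself names the test and assigns baseline data a descriptive role.

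Third, a reader might infer that the trial cannot say anything about its one-category target. That is too strong. A Hodges-Lehmann interval could be derived from the same test, though it is coarse, and the protocol attaches no success or exclusion rule to one category beyond sizing the trial.

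Fourth, the gain is undocumented. Power of 84%, 90% or 94% should not be promised: those are normal-theory figures, and the simulated ones are lower. At r = 0.3 there may be no gain. Baseline FAC, limited by eligibility to two values, would probably add little alone, so any useful gain depends on a measure such as FM-LE.

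**Conclusion.** The point holds as a matter of efficiency and interpretability, not validity. The protocol commits to an unadjusted comparison while collecting the covariates that could sharpen it, and the named test gives no result in the unit on which the trial was sized.

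Pre-specified adjustment would raise power by roughly 8 to 14 points if r is 0.5 to 0.6, and by −1 to +4 points at r = 0.3. This rests on an assumed SD of 0.95 to 1.5, an assumed correlation, and a one-category shift on a latent normal scale with 16 per arm. An interval for the FAC difference is useful whatever the correlation. The change is advisable because it is nearly free, but the trial is not unsound without it.

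**What to change.** - **Test.** Pre-specify one primary analysis of end-of-training FAC: a rank ANCOVA on treatment, baseline FM-LE and baseline FAC (0 or 1).
- **Estimate.** Report alongside it the adjusted mean FAC difference with 95% CI from a linear model with the same covariates, read against one category. Rank ANCOVA does not supply this itself, because its coefficient is in rank units.
- **Sensitivity.** Keep the unadjusted Mann-Whitney test.
- **Six months.** Use the same approach for six-month FAC. The aims section calls that outcome secondary, while the statistics section says "The primary outcome will be the FAC immediately after the training period and at six months after stroke"; its status should be settled in the same edit.
- **What to avoid.** Do not rely on a proportional-odds ratio for the one-category question. It is not in FAC categories, and at 16 per arm the upper limit of its simulated 95% interval was typically 15 to 27 times the lower.

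Fix the covariates before outcome data are seen, so that the choice cannot follow the results.

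**Cost.** A wording change and minor analysis work, with no added patients, visits or measurements. The downsides are two degrees of freedom, a negligible power loss if the covariates are not prognostic, and treating a six-level scale as numeric for the estimate.
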